### 2.8. Data Collection

As shown in Figure 1, women will be evaluated in three moments: baseline assessment (t0), immediately after program (t1) and one year after completion of treatment (t2). Assessment will take approximately 90 min. Information gathered will be kept under lock and key. To maintain the confidentiality of personal information, a coded ID number will be assigned to each participant.

### 2.9. Data Analysis

Since this study aims to determine the potential benefits of therapeutic exercise on the HRQoL of endometriosis patients, statistical analyses will be performed on an intention-to-treat basis. Only those participants that would have attended at least 75% of the sessions and completed at least two assessments (baseline and one evaluation of the two follow-ups) will be included in the analyses. The worst-case value will be used to replace missing data, after a previous reported procedure.

Mean and standard deviation will be used to describe variable scores at baseline and both follow-up measurements (postprogram and 1 year). Additionally, the Shapiro–Wilk test will be used to assess the normality of the distribution of the variables. To evaluate the ability of the randomization process to avoid differences between groups at baseline, Student’s t-test and chi-square test will be used to compare continuous and categorical data, respectively. An equivalent statistical approach will be conducted in case of non-parametrical data (Mann–Whitney and Kruskal–Wallis tests).

To evaluate the influence of treatment on outcome scores, a repeated-measure ANCOVA between the three time points (baseline, postprogram and 24 weeks later) will be used to examine the between-group and within-subject differences. Patient age, years since diagnosis, education level, marital status and the presence of heavy bleeding during the menstruation period will be used as covariates. To complete the analysis, we will report effect size (Cohen d) and level significance attending to interaction effects (group x time) to examine intergroup effects and to determine whether these were negligible (d < 0.2), small (0.2 < d > 0.5), moderate (0.5 < d > 0.8) or large (d > 0.8).

The statistical significance will be set at α = 0.05. Statistical analyses will be conducted on the Statistical Program for Social Sciences (IBM, SPSS 24.0).

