The second part of the intervention will lasts 8 weeks with group sessions twice per week focused on health-related fitness and motor control improvement. Each session will be divided into three sections: (1) an initial period with warm-up exercises (10 min); (2) a main period with aerobic (20–40 min) (continuous brisk walks), stretching (10–15 min) and lumbopelvic stabilization exercises (30–35 min) (taking into consideration the instructions previously learnt about motor control); and a final cool-down period of breathing and relaxation exercises. Details of the specific lumbopelvic stabilization exercises that these participants will perform are summarized in Table 1’s footnotes. Increases in both duration and intensity for aerobic exercises will be carried out based on fatigue perception. Alternatively, duration, intensity and number of repetitions for resistance exercises will be sequentially increased over time based on the adequate motor control of the lumbopelvic area, as well as fatigue perception. For that, by using the Borg Fatigue Scale [56], the physiotherapist (aided by two technicians) will daily inform about the maximum level of perceived fatigue that each patient must assume (from <11 at initial week to 13–14 at the end of the program), and thus, the women will increase or decrease the exercise intensity accordingly. For that purpose, women will be previously instructed with this scale to appropriately report their current perceived fatigue.

Adherence is defined based on the patient’s attendance to the sessions, considering as dropouts when they do not participate in at least 12 (75%) of 16 scheduled sessions. To maximize adherence, some strategies will be implemented, including adapted timetables to patient needs, music in all sessions and telephone calls following missed sessions.

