#### 2.3.2. Usual Care/Control Group

Participants randomly assigned to the control group (*n* = 13) will receive the usual treatment, which is stipulated by their gynaecologist. Additionally, during the initial evaluation session, the trained physiotherapist assessor will offer general advice about the positive effects of physical activity and a healthy lifestyle for their HRQoL. For ethical reasons, control participants will be given the opportunity to participate in an exercise program with the same characteristics of this therapeutic exercise intervention after completion of this study, although their results will not be included in the analyses.

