### 2.7. Randomization and Blinding

Once the baseline evaluation will be completed, participants will be included in either the therapeutic exercise intervention or the control group (1:1). For that, a computer-generated sample randomization sequence will be created by a researcher not involved in the clinical part of this study (Epidat 3.4, Xunta de Galicia, Spain). Once known, the primary investigator will communicate the assigned group to each participant. Therefore, although practitioners and participants will not be blinded, other researchers (assessors, statisticians and data managers) will be blind to group allocation. Participants will be asked not to mention any details of their treatment or their group allocation to the assessor(s) (responsible for evaluation sessions). If blinding is compromised, another assessor will be contacted and will complete the data collection.

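### The analysis is called intention-to-treat but drops women who attended under 75% of sessions, an exclusion that only the exercise arm can trigger

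*Protocol article*

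**What the plan says.** Section 2.9 (Data Analysis) of the protocol article states that "statistical analyses will be performed on an intention-to-treat basis". The sentence that follows defines who is analysed: "Only those participants that would have attended at least 75% of the sessions and completed at least two assessments", the two assessments being baseline and one of the two follow-ups. The same paragraph adds: "The worst-case value will be used to replace missing data, after a previous reported procedure".

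Section 2.3.1 (Exercise Intervention Group) defines adherence by attendance, "considering as dropouts when they do not participate in at least 12 (75%) of 16 scheduled sessions".

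Section 2.3.2 (Usual Care/Control Group) says that controls "will receive the usual treatment, which is stipulated by their gynaecologist", with general advice at the initial evaluation. They are offered the exercise programme only once the study is over, "although their results will not be included in the analyses".

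Section 2.7 (Randomization and Blinding) says that "other researchers (assessors, statisticians and data managers) will be blind to group allocation". The article describes no other analysis set that keeps every randomised woman.

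**The concern.** Two adjacent sentences describe different analysis sets. A set conditioned on attendance after randomisation is a per-protocol set, whatever it is called. Because attendance exists in one arm only, the filter is also one-sided: a selected group of good attenders would be compared with controls who passed no such filter. If the women who attend poorly are also those who improve least, the exercise arm looks better than it should, and the report would still describe the result as intention-to-treat. The rule decides who enters the primary comparison, and with 26 women the loss of a few from one arm matters.

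**Working it through.** **1. Which arm can fail the rule.** The rule has two conditions.

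| Condition (2.9) | Exercise arm | Control arm |
|---|---|---|
| At least 75% of sessions (12 of 16, since 0.75 × 16 = 12) | can fail | no sessions to count (2.3.2) |
| Baseline plus one follow-up | can fail | can fail |

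The second condition also departs from intention-to-treat, but it applies to both arms. The attendance condition is the one-sided one.

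**2. The plan's own figure (2.6).** Inputs are 28.4 ± 18.7 against 3.66 ± 18.4, α = 0.05 and power 85%. The pooled SD is √((18.7² + 18.4²)/2) = 18.55, so d = 24.74/18.55 = 1.33 (stated as 1.34). The two-sided normal approximation gives n = 2 × ((1.960 + 1.036)/1.34)² = 10.0 per arm, which matches the stated 10. The stated 30% allowance gives 10 × 1.3 = 13. These figures are used below as inputs only.

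**3. How many women the rule could remove.** If the planned 30% all fell below the attendance threshold, 0.30 × 13 = 3.9, or about 4 exercise women, would be removed and no controls. The comparison would be about 9 against 13.

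**4. Size of the bias with no true effect.** Assume that the lowest fraction f on an attendance score is removed from the exercise arm only, and that the score has correlation ρ with improvement in EHP-30. Neither quantity is in the documents. For a normal score, bias in SD units = ρ × φ(z_f)/(1 − f). The ratio is 0.350 at f = 0.2 and 0.497 at f = 0.3. Points use SD 18.55, assumed to be the SD of the quantity analysed.

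| ρ | f = 20% | f = 30% |
|---|---|---|
| 0 | 0 | 0 |
| 0.3 | 0.105 SD (1.95 points) | 0.149 SD (2.76 points) |
| 0.5 | 0.175 SD (3.25 points) | 0.248 SD (4.61 points) |
| 0.7 | 0.245 SD (4.54 points) | 0.348 SD (6.4 points) |

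**5. Type I error.** In simulations of a two-sided t-test with the 4 least adherent of 13 removed from the exercise arm (9 against 13, 100,000 runs per setting), rejection is 4.9% at ρ = 0, about 6% at 0.3, about 8.5% at 0.5 and about 12% at 0.7. False positives favouring exercise rise from 2.5% to about 5% at ρ = 0.3 and about 8% at ρ = 0.5.

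**6. When the bias vanishes.** Section 2.9 plans a repeated-measures analysis with a group × time interaction, so what matters is the link between attendance and change. If attendance tracks only a stable trait that shifts baseline and follow-up equally (baseline–follow-up correlation 0.6 assumed, 4 of 13 removed), the simulated bias in the change score is about 0 and rejection stays near 5%.

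**7. Power under a true intention-to-treat set.** With 13 against 13 and an exact two-sided t-test, power at d = 1.34 is 90.6%. If non-attenders gain nothing (an assumption), d becomes 1.34 × (1 − f):

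- f = 10%: d = 1.21, power 83.9%
- f = 20%: d = 1.07, power 74.6%
- f = 30%: d = 0.94, power 63.1%

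**The case against.** The contradiction in the text is hard to dispute, so the best case on the other side concerns what is built on it.

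- **Direction.** A reader might infer that the rule certainly favours exercise. The documents do not establish this. The adherence measures in 2.3.1 (flexible timetables, music, calls after missed sessions) point to scheduling and motivation as much as to symptoms, and the bias is zero if attendance is unrelated to change. On the other side, the Introduction links pain to reduced physical activity, so poor attenders may well be the women doing worse. That makes benefit the probable direction, but not a fact. This objection stands.
- **Size.** The top of the range needs a correlation of 0.7, which nothing in the article supports. At f = 20% and ρ = 0.3 the bias is about 8% of the planned difference (1.95/24.7). The figures are therefore a sensitivity range that starts at zero.
- **Controls.** Read literally, the rule would exclude every control. That cannot be meant, because 2.9 plans between-group comparisons. The conditional wording could be a hypothetical test applied to controls, but the article gives no way to determine it for them.
- **Blinding.** It is tempting to conclude that the rule unblinds the statistician. Section 2.7 does not say who applies it, and session staff could supply an inclusion flag. What remains is that attendance records exist in one arm only, so they can hint at allocation.
- **Follow-up.** The dropout label in 2.3.1 might suggest that poor attenders are no longer assessed. Section 2.8 plans three assessments and exempts no one, so no gap is documented. The label is only ambiguous.

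Two possible rescues fail. Worst-case imputation cannot help women who are not in the analysis. The non-inferiority label in 2.1 does not justify a per-protocol set, because the set is called intention-to-treat, no margin is given, and 2.6 sizes the trial to detect a difference.

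**Conclusion.** The point holds. The stated intention-to-treat analysis and the stated inclusion rule cannot both be carried out, and the attendance condition can remove women from the exercise arm only. This follows from the text alone and needs no assumption.

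The consequence is conditional. The primary result can be biased, probably towards benefit, if attendance predicts change in EHP-30. Under the assumptions in steps 4 and 5, the spurious benefit lies between 0 and about 0.35 SD (6.4 points), and two-sided type I error between 5% and about 12%. The documents do not support a firmer statement of direction or size. Blinding is a secondary matter. The rule should be corrected before analysis because it defines the primary comparison and the label would mislead readers.

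**What to change.** - In 2.9, make the primary analysis all randomised women in the arm assigned, whatever their attendance, using all available EHP-30 assessments. Delete the 75% rule from the primary set.
- Keep women who attended at least 12 of 16 sessions as a per-protocol sensitivity analysis, labelled as such.
- In 2.3.1, separate non-adherent women from women lost to assessment.
- Have someone other than the blinded statistician apply any set based on attendance.

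Cost: the changes are to wording and can be made without recruiting more women. The price is a possibly diluted effect. If 20–30% of the exercise arm do not attend and gain nothing, power at 13 per arm is 74.6% to 63.1% instead of the planned 85%. Restoring 85% under that assumption would take about 17 to 22 per arm (exact two-sided t-test), so the team should decide whether to accept the loss or enlarge the trial.

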#### 2.4.1. Primary Outcome: Health-Related Quality of Life

HRQoL will be addressed through the Spanish version of the Endometriosis Health Profile-30 (EHP-30) [57,58], a 30-item, disease-specific tool to evaluate HRQoL in women with endometriosis with high reliability (Cronbach’s α ranged between 0.79 and 0.97). It contains a total of five domains (pain, control and powerlessness, emotional well-being, social support and self-image), and items within each domain, answered on a 5-point Likert-type scale, are summed and transformed to a percentage scale. Scoring ranges from 0 to 100, with higher scoring representing a worse health status.

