### 2.6. Sample Size

The estimated sample size was determined for the primary outcome variable (HRQoL-pain) using the EHP-30 questionnaire and calculations from a previous study to detect a mean difference between control and intervention groups of 24.7 (28.4 ± 18.7 vs. 3.66 ± 18.4; Gonçalves, Barros and Bahamondes [40]). Assuming an α error of 0.05, a power of 85% and an effect size of 1.34 (based on the results of the reference study), we need a sample of 10 participants for each group. Assuming a possible 30% dropout rate, we will recruit a minimum of 13 participants per group (*n* = 26). G*Power v. 3.1 (Düsseldorf University, Düsseldorf, Germany) was used to calculate the sample size.

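### Filling a missed follow-up score with an undefined worst-case value can cost much of the power and, if loss is clearly unequal between arms, bias the effect in either direction

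*Protocol article*

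**What the plan says.** The whole missing-data provision is one sentence in section 2.9 of the protocol article: "The worst-case value will be used to replace missing data, after a previous reported procedure". No value is specified and no reference is attached to the earlier procedure. The article gives no other method.

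The same paragraph limits who can be imputed. It states that "statistical analyses will be performed on an intention-to-treat basis", but then restricts the analysis: "Only those participants that would have attended at least 75% of the sessions and completed at least two assessments", meaning baseline and either follow-up. A woman with no follow-up is left out. A woman in the analysis can lack at most one of the two follow-up scores, plus stray items or tests.

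For the primary outcome, section 2.4.1 says: "Scoring ranges from 0 to 100, with higher scoring representing a worse health status". The worst value the scale allows is therefore 100. The treatment effect is judged by a repeated-measures ANCOVA over three time points, through the group-by-time interaction and Cohen's d.

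**The concern.** A single extreme value entered as if it had been measured does two things. It moves an arm's mean in proportion to the share of women imputed, and it widens the spread. If loss is equal in the two arms, the estimated effect shrinks while its standard error grows. If loss is unequal, the arm with more missed visits looks worse whatever exercise does. The rule is therefore not reliably conservative: extra loss among controls favours exercise, and extra loss among exercisers works against it.

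Unequal imputation is possible under this plan. Only the exercise arm has sessions, so the attendance filter can remove women only there, while a control who misses one visit can stay in and be imputed. With 13 women per arm, one or two imputed scores already matter. Because Cohen's d grades the result, distortion of both the difference and the SD also feeds into the reported label.

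**Working it through.** **Inputs from the article.** Section 2.6: 28.4 ± 18.7 versus 3.66 ± 18.4, "Assuming an α error of 0.05, a power of 85% and an effect size of 1.34", 10 evaluable and 13 recruited per group. Section 2.9: "The statistical significance will be set at α = 0.05", taken as two-sided. Section 2.4.1: scale 0–100, higher is worse.

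**Assumptions not in the article.** Control mean 50 (40–60 also tried), within-woman correlation 0.5, loss at one follow-up visit unrelated to outcome, scores clipped to 0–100, planned covariates omitted.

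**The plan's own figure.** Difference 28.4 − 3.66 = 24.74. Pooled SD √((18.7² + 18.4²)/2) = 18.55. d = 24.74/18.55 = 1.33. Normal approximation: 2 × ((1.960 + 1.036)/1.34)² = 10.0 per group, as stated. The exact two-sided t calculation gives power 0.81 at 10 per group and needs 12 for 85%, so there is little reserve.

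**Arithmetic of the rule, imputing 100.** If a share p of an arm with mean μ and SD σ is set to 100, the mean moves by p(100 − μ), and the variance becomes (1 − p)σ² + p(1 − p)(100 − μ)².

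- One of 13 controls: 50/13 = 3.8 points, or 16% of 24.74.
- Three of 13 in each arm (p = 0.231), before clipping: difference 24.74 × 10/13 = 19.0. Control SD √(264.7 + 443.8) = 26.6. Exercise SD (mean 25.26) √(264.7 + 991.7) = 35.4. Pooled SD 31.3. Cohen's d drops from 1.33 to 19.0/31.3 = 0.61, from large to moderate on the article's own grading.
- No effect, 0 exercise versus 3 control missing: 3/13 × 50 = 11.5 points of false benefit. 0 versus 4: 15.4. 1 versus 3: 2/13 × 50 = 7.7.
- True effect, 3 exercise versus 0 control missing: 24.74 − 3/13 × 74.74 = 7.5 (7.0 in simulation, after clipping).

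**Simulated power of the group-by-time test** (13 per arm, true difference 24.74, control mean 50):

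| Missing per arm | Observed data only | Imputed at 100 | Imputed at worst observed |
|---|---|---|---|
| 0 | 0.93 | – | – |
| 1 | 0.90 | 0.74 | 0.83 |
| 3 | 0.85 | 0.37 | 0.64 |

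For control means of 40–60, the three-missing results run over 0.20–0.52 (scale worst) and 0.60–0.67 (worst observed).

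**Simulated results with no true effect:**

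| Missing, exercise vs control | Spurious benefit: at 100 / worst observed | Two-sided false-positive rate |
|---|---|---|
| 0 vs 3 | 11.5 / 8.1 points | about 12–18% |
| 0 vs 4 | 15.3 / 10.8 points | about 21–31% |
| 1 vs 3 | 7.7 / 5.4 points | near 5% |

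At 1 versus 3 the inflated variance offsets the bias in the test, but not in the estimate. Observed data alone gave no bias and about 5% error throughout.

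**Own-worst reading.** With the woman's own worst earlier score and three missing per arm, group-by-time power is 0.89. At 0 versus 3 with no effect, the bias is 1.6 points and the error rate 0.058.

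**The case against.** The strongest reply concerns scope. A reader might infer that every missing outcome is replaced, and that "Assuming a possible 30% dropout rate" in section 2.6 is the share of scores to be imputed. The article does not support that. Section 2.3.1 defines dropouts by session attendance, and such women leave the analysis set, as do women without any follow-up. No figure in the article gives a rate of missed visits among those analysed, so three or four of 13 is an upper case. This stands. One missing per arm is a modest scenario, and there the cost is smaller but still visible.

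Second, a t-test at a single follow-up exaggerates the loss: with three missing per arm it gives 0.12 and 0.43, where the planned type of test gives 0.37 and 0.64. That is why the group-by-time figures are used here.

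Third, the term is undefined and may mean something milder. This also stands: under the own-worst reading there is little to object to. A condensed article may leave the definition and its source to a fuller document, so the missing citation is not itself the point. But the sentence as written admits all three readings, and the results differ greatly between them.

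Fourth, the simulation assumes loss unrelated to outcome, which favours observed-data methods. If women miss visits because they are doing badly, observed data are biased too. That argues for a sensitivity analysis, not for an extreme value as the main method.

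**Conclusion.** The concern holds within limits. As the sole stated method, worst-case replacement is a poor choice for the primary analysis if it means the scale maximum or the worst observed score. It then costs about 0.07 to 0.16 of power with one missing per arm, compared with using observed data (0.90 against 0.83 or 0.74). In the upper case of three per arm it costs about 0.21 to 0.48 (0.85 against 0.64 or 0.37). Markedly greater loss among controls creates false benefit and false positives. Greater loss among exercisers masks benefit.

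Three stronger readings are not supported. The rule does not always inflate type I error: this needs marked imbalance, and at 1 versus 3 the rate stays near 5%. It is not shown that missed visits would outweigh the effect of exercise: with one missing per arm the estimate moves only from about 24 to 24 × 12/13 = 22. Nor does the article show that controls will be lost more often. The offer of the programme after the study could equally encourage them to stay.

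The sizes rest on the assumed control mean, correlation and outcome-unrelated loss. The direction did not change for control means of 40 to 60.

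**What to change.** In section 2.9, replace the sentence. Make the primary analysis a likelihood-based mixed model for the post-programme and one-year EHP-30 scores, using all observed outcomes and no single imputation. Keep worst-case replacement as a sensitivity analysis, with the value defined before data are seen. Run it symmetrically in both arms and then in one arm at a time, to show how far missing scores could move the result. Which women belong in the analysis set is a separate question that this change does not settle.

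The cost is analysis wording only: no extra patients or visits, and the named SPSS version can fit the model. The price is reliance on a missing-at-random assumption, which the sensitivity analysis is there to probe.

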### 2.3. Intervention

#### 2.3.1. Exercise Intervention Group

‘Physio-EndEA’ is a 9 (1 + 8)-week supervised tailored program of therapeutic exercise that incorporates global and lumbopelvic exercises that was designed by a multidisciplinary team. It combines aerobic, resistance and stretching exercises with a core stabilization perspective. The intervention will be performed in small groups of 4–6 participants, training 90 min/session twice a week. Sessions are designed, carefully supervised, guided and instructed by a qualified group of physiotherapists and physical exercise specialists with more than 5 years of experience in therapeutic exercise in oncology and related diseases.

The intervention planning is shown in Table 1. The first part of the program, with a single week duration, consists of individual sessions for initial training of motor control by using both rehabilitative ultrasound imaging (RUSI) [53] and a Stabilizer^®^ Pressure Biofeedback (Chattanooga, Hannover, Germany). For that, patients will be initially RUSI-guided to selective pre- or co-activate both TrA and pelvic floor muscles through the abdominal drawing-in manoeuvre (ADIM), as previously suggested [54,55]. This method facilitates both patient learning and clinician verification of TrA muscle recruitment pattern. After that, a trained physiotherapist teaches a sort of stabilization exercises with and without Stabilizer^®^. Patients are invited to repeat this list of exercises twice daily (>5 min each) during that week. Patient will not progress to the second part of the program until the physiotherapist verifies motor control with RUSI through the ability to pre-/co-activate and maintain contraction of TrA and pelvic floor muscles during basic lower-limb exercises. Moreover, during the following 2 weeks, patients are encouraged to continue with home-based biofeedback exercises.

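### Only the exercise arm is treated in shared groups, but the sample size and primary ANCOVA assume independent women; if outcomes correlate within training groups, the between-arm standard error will be too small

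*Protocol article*

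**What the plan says.** Randomisation is individual and 1:1 (section 2.7). Delivery differs between the arms:

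- **Exercise arm (section 2.3.1).** "The intervention will be performed in small groups of 4–6 participants, training 90 min/session twice a week". The first week is the exception: it "consists of individual sessions for initial training of motor control". After that, "The second part of the intervention will lasts 8 weeks with group sessions twice per week".
- **Control arm (section 2.3.2).** These women "will receive the usual treatment, which is stipulated by their gynaecologist", plus general advice at the first evaluation. They are not grouped.

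The sample size in section 2.6 is a two-group calculation in G*Power. Its basis is "a mean difference between control and intervention groups of 24.7 (28.4 ± 18.7 vs. 3.66 ± 18.4" and its settings are "Assuming an α error of 0.05, a power of 85% and an effect size of 1.34", leading to "we need a sample of 10 participants for each group" and to at least 13 recruited per arm. No ICC or design effect is among the inputs.

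For the analysis, section 2.9 states that "a repeated-measure ANCOVA between the three time points (baseline, postprogram and 24 weeks later) will be used to examine the between-group and within-subject differences". The five covariates are all characteristics of the individual woman. No training-group term, random effect or cluster-robust error is named.

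**The concern.** This is a partially nested design: women in one arm share sessions, setting and company for eight weeks, and women in the other arm do not. A repeated-measures model handles the correlation between one woman's own scores. It does not handle correlation between different women in the same training group.

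The primary outcome is self-reported and participants know their allocation (sections 2.4.1 and 2.7), so a shared group experience could plausibly move EHP-30 scores together. In that case the exercise arm carries less information than 13 independent women would, confidence intervals come out too narrow, and the nominal 0.05 is exceeded. With so few groups, one unusually good or poor group could shift the arm mean, and the planned analysis would not show it. What is at stake is how firmly a borderline result can be stated.

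**Working it through.** **1. The plan's own figure.** Pooled SD = √((18.7² + 18.4²)/2) = √344.1 = 18.55. Effect size = 24.7/18.55 = 1.33, against the stated 1.34. For two independent means with d = 1.34 and alpha 0.05, the noncentral t gives:

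- one-sided: 9 per arm for 85% power (85.9%); 10 per arm gives 89.2%;
- two-sided: 12 per arm for 85% power (88.0%; 11 gives 84.8%); 10 per arm gives 80.9%.

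The stated 10 lies within two women of either figure. It is a calculation for independent women.

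**2. Number of training groups.** With 13 women and sizes of 4 to 6, two groups hold at most 12 and four need at least 16, so three fit, for example 5, 4 and 4. The abstract's total of 22 would give 11 per arm and two groups.

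**3. Standard error.** Let m be the size of each group and n the size of the exercise arm. The design effect in that arm is DE = 1 + (Σm²/n − 1) × ICC. The control arm has DE = 1. With equal arms and equal variances, true SE / SE assuming independence = √((DE + 1)/2).

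For 5, 4 and 4: Σm²/n = (25 + 16 + 16)/13 = 57/13 = 4.385, so DE = 1 + 3.385 × ICC. At ICC 0.05, DE = 1.169 and the ratio is √(2.169/2) = 1.04.

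**4. False-positive rate.** This comes from 200,000 simulated trials per setting, with groups of 4, 4 and 5 against 13 independent controls, one post-treatment score, and a two-sided t-test that ignores groups. The ICC values are assumptions.

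| Assumed ICC | DE, exercise arm | SE ratio | Two-sided false-positive rate |
|---|---|---|---|
| 0 | 1.00 | 1.00 | 5.0% |
| 0.01 | 1.03 | 1.01 | 5.1% |
| 0.05 | 1.17 | 1.04 | 6.0% |
| 0.10 | 1.34 | 1.08 | 7.0% |
| 0.20 | 1.68 | 1.16 | 9.2% |

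With the abstract's 11 per arm in groups of 6 and 5, Σm²/n = 61/11 = 5.545. The SE ratio is then √((1.227 + 1)/2) = 1.06 at ICC 0.05 and √((1.909 + 1)/2) = 1.21 at ICC 0.20.

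**5. Sample size, design effect only.** With groups of 5, two-sided, 85% power and d = 1.34, the need per arm is 12, 13, 14 and 16 at ICC 0.01, 0.05, 0.10 and 0.20. Without clustering it is 12.

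**6. Power, and why it is not the measure of harm.** With 13 per arm at ICC 0.05, the test that ignores groups has about 90% power, and a test on three group means has about 75%. At ICC 0 the figures are already 91% and 79%. So about 12 of the 15 points are the price of having two between-group degrees of freedom. A t-test that multiplies the exercise-arm variance by DE at an assumed ICC of 0.05 has 88% power. Its simulated false-positive rate is 5.1% to 5.4% when the assumed ICC is right.

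**The case against.** The strongest reply is that nothing here is certain to be wrong. The documents give no ICC, and several features could make it small: the first week is individual, progression is set for each woman from perceived fatigue and motor control, timetables are fitted to patients' needs, and the last assessment comes long after training ends. All of this stands, and it is why the point is conditional and the range starts at 0.01.

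A reader might infer more than the text supports:

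- **That the standard error is too small as a matter of fact.** It is so only if outcomes within training groups are positively correlated.
- **That each group has its own physiotherapist, that groups are closed, or that there are exactly three.** Section 2.3.1 does not say so. It refers to one physiotherapist with two technicians, and staff who lead every group add no variation between groups. Section 2.6 sets 13 as a minimum, and the abstract's total would give two groups.
- **That the treatment estimate is biased.** Zero-mean differences between groups add variance, not bias, and training in company is part of the intervention under test.
- **That clustering costs 15 points of power.** Most of that belongs to a three-cluster test that is not recommended here.

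It can also be said that a sensitivity analysis of this kind is often left to an analysis plan. That is fair for the detail. But the article itself fixes the model, covariates, alpha and sample-size inputs, and as fixed they assume independence while section 2.3.1 describes shared delivery.

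**Conclusion.** The concern holds in conditional form. Treatment is given in groups in one arm only, and both section 2.6 and section 2.9 treat all women as independent. If outcomes correlate within training groups, the true between-arm standard error exceeds the reported one by about 1% to 8% for an ICC of 0.01 to 0.10, and by about 16% at 0.20. The two-sided false-positive rate then runs from about 5.1% to 7%, and to about 9% at 0.20. At ICC 0 nothing is wrong.

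These figures assume 13 women per arm in groups of 5, 4 and 4 with stable membership. They rest on a single post-treatment score, not the full three-time ANCOVA, where the relevant quantity would be the ICC of change. The effect is modest at low ICC. It would matter mainly for a result close to the significance boundary.

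**What to change.** - **Data collection:** record the training group of every exercise participant. Without this the question may be impossible to examine later.
- **Section 2.9:** keep the planned analysis as primary. Add a prespecified sensitivity analysis of the between-arm EHP-30 contrast, for example change from baseline to post-programme. In it, multiply the exercise-arm variance of the mean by 1 + (Σm²/n − 1) × ICC, using the group sizes actually analysed, at ICC 0.01, 0.05, 0.10 and 0.20. Call a significant result robust only if it holds across the plausible range, named in advance.
- **Section 2.6:** state that the calculation assumes no training-group effect.

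An assumed ICC is better kept out of the primary p-value, because the documents give no source for one and about three groups are too few to estimate it well.

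The cost is one recorded variable, a sentence or two in each section and a little more analysis, with no extra participants or visits. In the sensitivity results the confidence interval is about 4% wider at ICC 0.05 and up to about 16% wider at 0.20.
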